**Based on the assessment of the inclusion/exclusion criteria, the healthy volunteer may be admitted to the study: YES/NO**

If the volunteer continues the trial, the date of the next visit is \_\_. \_\_. \_\_\_\_

**Investigator:** \_\_\_\_\_  
*Name Surname* *Signature*

**Date:** « \_\_\_\_ » \_\_\_\_\_ 2020

## Visit 1 (Treatment period)

### Study day 1

Date of the visit \_ \_ . \_ \_ . \_ \_ \_ \_

#### Physical examination:

Body temperature \_ \_ °C

Swollen lymph nodes: YES/NO

If yes, underline which nodes are affected: occipital, posterior cervical, parotid, anterior cervical, submandibular, sublingual, supraclavicular and subclavian, axillary, epitrochlear, inguinal, popliteal.

Pharyngeal examination: hyperemia YES/NO

BP sitting \_ \_ / \_ \_ (mm Hg)

HR \_ \_ per min

RR \_ \_ per min

Wheezing in the lungs (dry/wet): YES/NO

If yes, describe nature and location \_\_\_\_\_

Abdominal palpation: soft, painless YES/NO

Liver: aligned with the costal arch: YES/NO

If no, describe in detail \_\_\_\_\_

Spleen: not enlarged YES/NO

If not, describe in detail \_\_\_\_\_

Tested with PCR for SARS-CoV-2 RNA: YES/NO

If yes, indicate the results \_\_\_\_\_

Current therapy: YES/NO

If yes, describe in detail the pharmaceuticals and daily doses \_\_\_\_\_

Assessment of adverse events: YES/NO

If yes, describe in detail the nature of the adverse event \_\_\_\_\_

#### Assessment of inclusion/exclusion criteria

##### Inclusion criteria

Healthy volunteers aged between 18 and 80 years: YES/NO

Informed consent form signed by the healthy volunteer: YES/NO

Ability of a volunteer to cooperate adequately (the volunteer can understand the information provided regarding the study and is willing to comply with the requirements of the study protocol): **YES/NO**

### **Exclusion criteria**

Healthy volunteers cannot be included in the trial if they meet at least one of the following criteria.

#### Criteria related to the underlying disease:

Detection of SARS-CoV-2 virus RNA by polymerase chain reaction (PCR) for COVID-19 in biomaterial samples and positive reactivity of enzyme-linked immunosorbent assay (ELISA) IgM and ELISA IgG to the virus in a healthy volunteer: **YES/NO**

Criteria related to the combination medication products, previous therapy and concomitant therapy: **YES/NO**

Hypersensitivity or individual intolerance to the components of the combination medication products according to the medical history: **YES/NO**

#### Criteria related to the concomitant pathology:

According to the medical history and physical examination: **YES/NO**

Any diseases or conditions that, in opinion of the investigator, would make it difficult to interpret the results of treatment or may limit the participation of a healthy volunteer in the study: **YES/NO**

#### According to screening laboratory tests:

Related to the compliance of healthy volunteers in the study: **YES/NO**

Any other diseases or conditions that, in the opinion of the investigator, would make it difficult to interpret the results of treatment or may limit the participation of a healthy volunteer in the study: **YES/NO**

Healthy volunteers who, in the opinion of the investigator, are obviously or likely unable to understand and evaluate the information regarding this study within the process of signing the informed consent form, in particular regarding the expected risks and possible discomfort: **YES/NO**

The inability or unwillingness of a healthy volunteer to follow the rules for carrying out the study and participating in a clinical trial: **YES/NO**

**Based on the assessment of the inclusion/exclusion criteria, the healthy volunteer may be admitted to the study: YES/NO**

### **Assessment of exclusion criteria**

A healthy volunteer will be excluded from the study if SARS-CoV-2 virus RNA is detected in biomaterial samples by a polymerase chain reaction (PCR) for COVID-19 or if there is positive reactivity to enzyme-linked immunosorbent assay (ELISA) IgM and ELISA IgG: **YES/NO**

A healthy volunteer may withdraw their consent to participate in the study at any time and without giving reasons. The investigator may also decide on early discontinuation of the participation of a healthy volunteer in the study at any time if the patient's condition requires it: **YES/NO**

Main reasons for early discontinuation of participation of a healthy volunteer in the study: **YES/NO**

Individual intolerance to the combination medication products or any of its components: **YES/NO**

Failure to meet the inclusion/exclusion criteria: **YES/NO**

Refusal of a healthy volunteer from participation in the study/withdrawal of informed consent by a healthy volunteer: **YES/NO**

Development of AEs that prevent further prophylactic therapy with the combination medication products: **YES/NO**

Emergence of a serious adverse event in a healthy volunteer: **YES/NO**

The emergence of exclusion criteria in the course of the study: **YES/NO**

Any condition of a healthy volunteer that requires, in the opinion of the investigator, the withdrawal of the patient from the study: **YES/NO**

Discontinuation of the trial by the research center, investigator, or regulatory authority: **YES/NO**

**Patient meets all the criteria of the study: YES/NO**

If not, specify the reason in detail \_\_\_\_\_

If the volunteer continues the trial, the date of the next visit is \_\_. \_\_. \_\_\_\_

**Investigator:** \_\_\_\_\_  
*Name Surname*

\_\_\_\_\_  
*Signature*

**Date:**     « \_\_\_\_ » \_\_\_\_\_ 2020

## Visit 2 (Treatment period)

### Study day 7

Date of the visit \_ \_ . \_ \_ . \_ \_ \_ \_

#### Physical examination:

Body temperature \_ \_ °C

Swollen lymph nodes: YES/NO

If yes, underline which nodes are affected: occipital, posterior cervical, parotid, anterior cervical, submandibular, sublingual, supraclavicular and subclavian, axillary, epitrochlear, inguinal, popliteal.

Pharyngeal examination: hyperemia YES/NO

BP sitting \_ \_ / \_ \_ (mm Hg)

HR \_ \_ per min

RR \_ \_ per min

Wheezing in the lungs (dry/wet): YES/NO

If yes, describe the nature and location

---

Abdominal palpation: soft, painless YES/NO

Liver: aligned with the costal arch: YES/NO

If no, describe in detail \_\_\_\_\_

Spleen: not enlarged YES/NO

If not, describe in detail \_\_\_\_\_

#### Specific laboratory diagnostics:

Tested with PCR for SARS-CoV-2 RNA: YES/NO

If yes, indicate the results \_\_\_\_\_

Current therapy: YES/NO

If yes, describe in detail the pharmaceuticals and daily doses \_\_\_\_\_

Assessment of adverse events: YES/NO

If yes, describe in detail the nature of the adverse event \_\_\_\_\_

#### Assessment of exclusion criteria

A healthy volunteer was excluded from the study if SARS-CoV-2 virus RNA was detected in biomaterial samples by polymerase chain reaction (PCR) for COVID-19 or if it was positive in enzyme-linked immunosorbent assay ELISA IgM and ELISA IgG: **YES/NO**

A healthy volunteer may withdraw their consent to participate in the study at any time and without giving reasons. The investigator may also decide on early discontinuation of the participation of a healthy volunteer in the study at any time if the patient's condition requires it: **YES/NO**

Main reasons for early discontinuation of the participation of a healthy volunteer in the study: **YES/NO**

Individual intolerance to the combination medication or any of its components: **YES/NO**

Failure to meet the inclusion/exclusion criteria: **YES/NO**

Refusal of a healthy volunteer to participate in the study or the withdrawal of informed consent by a healthy volunteer: **YES/NO**

Development of AEs that would prevent further prophylactic therapy with the combination medication: **YES/NO**

Emergence of a serious adverse event in a healthy volunteer: **YES/NO**

The emergence of exclusion criteria in the course of the study: **YES/NO**

Any condition of a healthy volunteer that requires, in the opinion of the investigator, the withdrawal of the patient from the study: **YES/NO**

Discontinuation of the trial by the research center, investigator, or regulatory authority: **YES/NO**

**Patient meets all the criteria of the study: YES/NO**

If not, specify the reason in detail \_\_\_\_\_

If the volunteer continues the trial, the date of the next visit is \_\_. \_\_. \_\_\_\_

**Investigator:** \_\_\_\_\_  
Name Surname

\_\_\_\_\_  
Signature

**Date:** « \_\_\_\_ » \_\_\_\_\_ 2020

## Visit 3 (Treatment period)

### Study day 14

Date of the visit \_ \_ . \_ \_ . \_ \_ \_ \_

#### Physical examination:

Body temperature \_ \_ °C

Swollen lymph nodes: YES/NO

If yes, underline which nodes are affected: occipital, posterior cervical, parotid, anterior cervical, submandibular, sublingual, supraclavicular and subclavian, axillary, epitrochlear, inguinal, popliteal.

Pharyngeal examination: hyperemia YES/NO

BP sitting \_ \_ / \_ \_ (mm Hg)

HR \_ \_ per min

RR \_ \_ per min

Wheezing in the lungs (dry/wet): YES/NO

If yes, describe the nature and location

---

Abdominal palpation: soft, painless YES/NO

Liver: aligned with the costal arch: YES/NO

If no, describe in detail \_\_\_\_\_

Spleen: not enlarged YES/NO

If not, describe in detail \_\_\_\_\_

#### Specific laboratory diagnostics:

Tested with PCR for SARS-CoV-2 RNA: YES/NO

If yes, indicate the results \_\_\_\_\_

Current therapy: YES/NO

If yes, describe in detail the pharmaceuticals and daily doses \_\_\_\_\_

Assessment of adverse events: YES/NO

If yes, describe in detail the nature of the adverse event \_\_\_\_\_

#### Assessment of exclusion criteria

A healthy volunteer will be excluded from the study if SARS-CoV-2 virus RNA is detected in biomaterial samples by a polymerase chain reaction (PCR) for COVID-19 or if there is positive reactivity to enzyme-linked immunosorbent assay (ELISA) IgM and/or IgG: **YES/NO**.

A healthy volunteer may withdraw their consent to participate in the study at any time and without giving reasons. The investigator may also decide on early discontinuation of the participation of a healthy volunteer in the study at any time if the patient's condition requires it: **YES/NO**

Main reasons for early discontinuation of the participation of a healthy volunteer in the study: **YES/NO**

Individual intolerance to the combination medication or any of its components: **YES/NO**

Failure to meet the inclusion/exclusion criteria: **YES/NO**

Refusal of a healthy volunteer to participate in the study or withdrawal of informed consent by a healthy volunteer: **YES/NO**

Development of AEs that would prevent further prophylactic therapy with the combination medication: **YES/NO**

Emergence of a serious adverse event in a healthy volunteer: **YES/NO**

The emergence of exclusion criteria in the course of the study: **YES/NO**

Any condition of a healthy volunteer that requires, in the opinion of the investigator, the withdrawal of the patient from the study: **YES/NO**

Discontinuation of the trial by the research center, investigator, or regulatory authority: **YES/NO**

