### **2.6. Exclusion Criteria**

Healthy volunteers cannot be included in the trial if they meet at least one of the following criteria.

2.6.1. Criteria related to the disease:

Detection of SARS-CoV-2 virus RNA by polymerase chain reaction (PCR) in biomaterial samples and/or positive enzyme-linked immunosorbent assay ELISA IgM and ELISA IgG to the virus in a healthy volunteer;

2.6.2. Criteria related to the combination medication, previous therapy and concomitant therapy:

Hypersensitivity or individual intolerance to the components of the combination therapy according to the medical history.

2.6.3. Criteria related to the concomitant pathology:

According to the medical history and physical examination:

- any diseases or conditions that, in opinion of the investigator, would make it difficult to interpret the results of treatment or may limit the participation of a healthy volunteer in the study.

According to screening laboratory tests:

- related to the compliance of healthy volunteers in the study;
- any diseases or conditions that, in opinion of the investigator, would make it difficult to interpret the results of treatment or may limit the participation of healthy volunteers in the study;

Healthy volunteers who, in the opinion of the investigator, are obviously or likely unable to understand and evaluate the information regarding this study within the process of signing the informed consent form, in particular regarding the expected risks and possible discomfort.

The inability or unwillingness of a healthy volunteer to follow the rules for carrying out the study and participating in a clinical trial.

2.7. **Early Discontinuation Criteria**

2.7.1. A healthy volunteer will be excluded from the study if SARS-CoV-2 virus RNA is detected in biomaterial samples by a polymerase chain reaction (PCR) for COVID-19 or if enzyme-linked immunosorbent assay (ELISA) IgM and ELISA IgG results are positive.

2.7.2. A healthy volunteer may withdraw their consent to participate in the study at any time and without giving reasons. The investigator may also decide on early discontinuation of the participation of a healthy volunteer in the study at any time if the patient's condition requires it.

2.7.3. Main reasons for early discontinuation of participation of a healthy volunteer in the study:

Individual intolerance to the combination medication or any of its components;

Failure to meet the inclusion and exclusion criteria;

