## 8. APPENDICES

### Appendix 1

|                                                                   | Study Plan |           |           |   |    |           |
|-------------------------------------------------------------------|------------|-----------|-----------|---|----|-----------|
|                                                                   | Procedures | Screening | Treatment |   |    | Follow-up |
|                                                                   | Visit      | 0         | 1         | 2 | 3  | 3 4       |
|                                                                   | Days       | -2 - 0    | 1         | 7 | 14 | 21±1 28±1 |
| Informed Consent                                                  |            | X         | -         | - | -  | -         |
| Insurance                                                         |            | X         |           |   |    |           |
| PCR for SARS-CoV-2 RNA                                            |            | X         | X         | X | X  | X         |
| ELISA IgM and IgG to SARS-CoV-2                                   |            | X         | -         | - | -  | X         |
| Demographics, Complaints and Medical History, Anthropometric Data |            | X         | X         | - | -  | -         |
| Inclusion and Exclusion Criteria Assessment                       |            | X         | X         | X | X  | X         |
| Physical Examination                                              |            | X         | X         | X | X  | X         |
| Vital Signs Assessment (BP, HR, RR, TEMP)                         |            | -         | X         | X | X  | X         |
| Exclusion Criteria Assessment                                     |            | X         | -         | - | -  | -         |
| Previous Therapy Assessment                                       |            | X         | X         | X | X  | X         |
| Concomitant Therapy Assessment                                    |            | X         | X         | X | X  | X         |

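### The antibody rule that ends participation differs between section 2.7.1 and the Day 14 and Day 21 forms, so a volunteer positive for one antibody class could lose the Day 28 outcome PCR

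*Protocol*

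**What the plan says.** Section 2.7.1 excludes a volunteer from the study on a positive PCR or "if enzyme-linked immunosorbent assay (ELISA) IgM and ELISA IgG results are positive". In Appendix 4, the Visit 1 form (Day 1) uses "positive reactivity to enzyme-linked immunosorbent assay (ELISA) IgM and ELISA IgG" and the Visit 2 form (Day 7) uses "positive in enzyme-linked immunosorbent assay ELISA IgM and ELISA IgG". The Visit 3 form (Day 14) and the Visit 4 form (Day 21) both use "positive reactivity to enzyme-linked immunosorbent assay (ELISA) IgM and/or IgG".

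The entry criterion in 2.6.1 joins the two classes with the same word as 2.7.1: "positive enzyme-linked immunosorbent assay ELISA IgM and ELISA IgG to the virus in a healthy volunteer".

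In the Study Plan (Appendix 1), the row "ELISA IgM and IgG to SARS-CoV-2" is marked at screening, dashed at Days 1, 7 and 14, and has one mark in a follow-up column headed with both Day 21±1 and Day 28±1. The row "PCR for SARS-CoV-2 RNA" is marked at screening, at each treatment visit and in the same follow-up column. The Day 14 and Day 21 forms have a result field for PCR ("Tested with PCR for SARS-CoV-2 RNA: YES/NO") but none for ELISA.

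The efficacy endpoint in section 2.2 is RT-PCR positivity within 28 days. Section 6 says that the data of all enrolled volunteers will be taken into account.

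**The concern.** The rule takes the volunteer out of the study, not merely off the product, so it decides who is still swabbed for the primary endpoint. Two texts of the same protocol give opposite instructions for the same antibody result, and nothing says which one governs. The looser wording appears at Days 14 and 21, when treatment is ending or over and the remaining efficacy information is the follow-up PCR.

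A newly detected single antibody class may reflect recent infection. If such volunteers are taken out before their last swab, the loss need not be random with respect to the endpoint. It would tend to lower the observed infection rate, which favours the product in a single-cohort comparison with a fixed 11.1%.

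**Working it through.** **1. The rules side by side (literal reading)**

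| Place | Antibody result that ends participation | Scheduled ELISA at that time |
|---|---|---|
| Section 2.7.1 | IgM and IgG | not tied to a visit |
| Visit 1 form, Day 1 | IgM and IgG | none |
| Visit 2 form, Day 7 | IgM and IgG | none |
| Visit 3 form, Day 14 | IgM and/or IgG | none |
| Visit 4 form, Day 21 | IgM and/or IgG | one mark for Days 21 and 28 together |

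**2. Which swabs could be lost**

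- *Day 14.* No ELISA is scheduled on Days 1, 7 or 14. A removal here would need the screening result to be applied again or an unscheduled test. Section 2.6.1, read literally, does admit a volunteer positive for one class, but the protocol does not describe re-use of that result.
- *Day 21.* If the follow-up ELISA is drawn at this visit, a single-class positive is removed under the form and kept under 2.7.1. The Day 21 PCR belongs to the same visit, so only the Day 28 PCR is at risk.
- *Day 28.* If the ELISA is drawn only then, no later swab remains to be lost.

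**3. The plan's own figure**

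Inputs from section 2.4: p0 = 0.111, p1 = 0.03, alpha 0.05, and 0.85, which reproduces the sample size only if read as power. For a one-sample test of a proportion, two-sided:

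n = [(1.960 × √(0.111 × 0.889) + 1.036 × √(0.03 × 0.97)) / (0.111 − 0.03)]² = [(0.6157 + 0.1768) / 0.081]² = 95.7, rounded up to 96.

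The stated 96 is reproduced, and this point does not change it. Expected events among 96 are 96 × 0.111 = 10.7 at the reference rate and 96 × 0.03 = 2.9 at the hoped-for rate.

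**4. Size of a Day 28 loss**

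The protocol states no decision cut-off. For illustration, take the largest event count whose lower-tail probability at 11.1% is at most 0.025. With 96 volunteers this is 4: P(X ≤ 4 | 96, 0.111) = 0.0145, against P(X ≤ 5) = 0.0376.

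The protocol gives no single-class positivity rate, so assume a share s of 2%, 5% or 10%, lost at random after Day 21, with a constant hazard over 28 days:

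- h = −ln(1 − 0.111) / 28 = 0.00420 per day
- probability of an event by Day 21 = 1 − exp(−21h) = 0.0845
- observed rate = (1 − s) × 0.111 + s × 0.0845
- expected events lost = 96 × s × (0.111 − 0.0845)

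| s | Volunteers (96 × s) | Observed rate | Expected events lost | P(X ≤ 4) |
|---|---|---|---|---|
| 0 | 0 | 11.10% | 0 | 1.45% |
| 2% | 1.9 | 11.05% | 0.05 | 1.51% |
| 5% | 4.8 | 10.97% | 0.13 | 1.60% |
| 10% | 9.6 | 10.83% | 0.25 | 1.76% |

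**5. A selective loss**

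If one true case goes undetected because its swab was not taken, five true events appear as four. The chance of seeing 4 or fewer is then P(X ≤ 5 | 96, 0.111) = 3.8%. This supposes that a case is lost; it does not estimate how often that would happen.

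**The case against.** The strongest objection is that the schedule prevents most of the harm. A reader might infer that volunteers are removed at Day 14 and so lose both the Day 21 and the Day 28 swab. The documents do not support that: Appendix 1 has no ELISA at Day 14, the Day 14 form has no field for one, and nothing tells the investigator to apply the screening result again. This part of the objection stands in full, and for that reason the working does not model the loss of both swabs.

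Even the Day 28 loss is conditional. The follow-up column is merged in the text at hand, the Day 21 form has no ELISA field, and a case is missed only if its first positive PCR would have come at Day 28. This also stands. Still, the ELISA mark sits in the same merged column as the PCR and the physical examination, both of which the Day 21 form records, so an ELISA at Day 21 is a fair reading, though not a certain one.

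A reader might also take section 6 to mean that a removed volunteer without a positive PCR counts as uninfected. It says only that the data of all enrolled volunteers are taken into account; how incomplete follow-up is counted may be settled in an analysis plan that is not at hand.

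Finally, the word joining the two classes in 2.7.1 may have been meant loosely, with either class sufficient. If so, 2.7.1 and the early forms are ambiguous and the later forms are not. The texts would still need aligning.

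**Conclusion.** The contradiction is certain on a literal reading: 2.7.1 and the Day 1 and Day 7 forms need both classes, while the Day 14 and Day 21 forms need one. Its effect on the endpoint is possible rather than established. A volunteer positive for one class could be removed at Day 21 before the Day 28 PCR if the follow-up ELISA is drawn at Day 21, and at Day 14 only if a screening or unscheduled result is used.

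With random loss of the Day 28 swab in 2% to 10% of 96 volunteers, the chance of 4 or fewer events at a true 11.1% moves from 1.45% to between 1.5% and 1.8%, which is slight. One case lost through selective removal would take it to 3.8%, above the 2.5% lower tail implied by the two-sided design that reproduces the sample size. These figures rest on the assumed positivity range, a constant hazard and an illustrative cut-off, none of which the protocol gives. The point merits correction because the rule decides who remains under primary-endpoint follow-up and the correction is nearly free, not because a large bias has been shown.

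**What to change.** Reconcile the antibody wording in section 2.7.1 and on every visit form in Appendix 4, and show in the ELISA row of Appendix 1 whether the follow-up sample is taken at Day 21, Day 28 or both. Which antibody rule applies is for the sponsor to decide; this point takes no view on it or on any treatment decision.

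Add one sentence to the protocol: after an antibody result without a positive PCR, the remaining scheduled outcome PCRs are still collected and counted towards the 28-day endpoint, whatever is decided about other participation.

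The cost is corrected wording on the affected pages, a clearer schedule row and one new sentence. The PCRs are already scheduled, so no extra swabs are added.
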